Recent advances in neuroimaging provide powerful tools to explore acupuncture-induced neuroplasticity (9). The spontaneous neural activity and functional connectivity of the brain's internal network can be assessed by resting-state functional MRI (rs-fMRI), and white matter connectivity and its microstructure can be assessed by diffusion tensor imaging (DTI). However, research on the mechanisms of brain functional network remodeling underlying acupuncture treatment for PSD is still insufficient. Rs-fMRI quantifies intrinsic activity (e.g., ALFF, ReHo) and functional connectivity to track network-level functional reorganization after stroke (10, 11). DTI evaluates white-matter microstructure (e.g., FA, MD) and can delineate structural disconnections within swallowing networks (12, 13). In post-stroke dysphagia, neural recovery is thought to involve both functional reorganization of swallowing-related networks and structural remodeling of white-matter pathways. Thus, investigating the interaction between structural and functional networks may provide insights beyond analyses of structural or functional alterations alone (14). Previous imaging studies of PSD have not focused on the interaction between functional and structural remodeling in swallowing-related networks, but only on changes in local activation.

To address this gap, we designed a single-blind, randomized, sham-controlled trial to elucidate the clinical efficacy and neural mechanism of Tiao Shen Li Yan acupuncture in treating PSD. By prespecifying multimodal neuroimaging endpoints—namely, rs-fMRI and DTI—the study aims to characterize how acupuncture modulates brain network organization during swallowing recovery. Specifically, we hypothesize that Tiao Shen Li Yan acupuncture enhances integration within swallowing-related functional networks, promotes microstructural repair of white-matter pathways, and strengthens structure-function coupling, thereby facilitating functional reorganization of brain networks and ultimately improving swallowing function and quality of life in patients with PSD.

This protocol adheres to the SPIRIT 2013 Statement and CONSORT guidelines for clinical trial design and reporting. The findings are expected to provide mechanistic evidence for acupuncture-induced neuroplasticity and to support the development of standardized, evidence-based rehabilitation strategies for PSD.

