#### fMRI data analysis

2.11.1

Preprocessing and analyses will be conducted with SPM12, DPABI, and FSL. Functional and structural connectivity will be analyzed using independent component analysis (ICA) and canonical correlation analysis (CCA) (43–45). ROI-based analyses will prioritize prespecified swallowing-related hubs (the insula, basal ganglia, frontal cortex, M1, SMA, corona radiata, and S1) as the primary ROI set for functional and structural connectivity tests. Network-level extensions (e.g., the default mode network (DMN), the frontal-temporal-sensory-motor circuit, the sensory-motor-insular-thalamic circuit and the insula-cerebellum-occipital circuit) will be reported as secondary/supportive analyses with appropriate multiple-comparison control. Structure–function coupling will be assessed by examining the relationship between functional connectivity and structural connectivity between corresponding brain regions. Functional connectivity (FC) will be calculated as the Pearson correlation between the BOLD time series of predefined regions of interest (ROIs). Structural connectivity will be derived from diffusion tensor imaging using probabilistic tractography to identify white-matter fiber tracts connecting the same ROI pairs. For each tract, the mean fractional anisotropy (FA) along the reconstructed fibers will be calculated to represent the integrity of the structural pathway. Structure–function coupling will then be evaluated by assessing the relationship between FC strength and tract-specific FA values across ROI pairs (46). In addition to the hypothesis-driven ROI analyses, exploratory whole-brain analyses will be conducted to identify potential PSD-related brain regions beyond the predefined swallowing network. Voxel-wise comparisons of rs-fMRI metrics (e.g., ALFF and ReHo) will be performed across the whole brain between groups. Statistical analyses will be conducted using a general linear model framework, and multiple comparisons will be controlled using false discovery rate (FDR) correction (p < 0.05). This will allow us to assess how acupuncture modulates the interaction between structural integrity and functional network organization in PSD.

To correct for multiple comparisons, we will apply the false discovery rate (FDR) at the voxel level and Bonferroni correction for network-level metric (47).

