We hypothesize that the Tiao Shen Li Yan acupuncture may improve swallowing function in PSD by enhancing integration within swallowing-related functional networks and promoting microstructural repair of inter-network white-matter pathways, thereby strengthening structure-function coupling across swallowing networks and facilitating functional reorganization of brain networks. In addition to the predefined ROI-based analyses, exploratory whole-brain analyses will also be performed to identify potential PSD-related brain regions that may not be included in the current swallowing network framework. These regions could become targets for future investigations. Importantly, structural and functional connectivity do not necessarily change in parallel during post-stroke recovery. Improvements in functional connectivity in the absence of structural recovery may reflect compensatory reorganization rather than true restoration (62), whereas structural recovery without corresponding functional gains may indicate suboptimal recovery. Therefore, quantifying structure–function coupling may provide mechanistic insight beyond assessing functional or structural metrics alone, by characterizing whether and how functional network reorganization remains constrained by (or diverges from) the underlying structural scaffold.

Overall, a major strength of this study is that it combines rs-fMRI and DTI to establish an “imaging-to-clinic” evidence chain that closely links clinical efficacy with mechanistic evidence. This approach is intended to delineate the structure-function coupling mechanisms by which the Tiao Shen Li Yan acupuncture modulates swallowing networks in PSD, and reveal the mechanism of brain functional network reorganization in PSD patients through acupuncture, while the inclusion of healthy controls enhances clinical relevance and interpretability.

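### The coupling measure tracks how FC and FA patterns align, not how good either is, so a rise in coupling cannot by itself be read as benefit

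*Protocol article*

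**What the plan says.** Section 2.11.1 builds coupling from two quantities per ROI pair. FC "will be calculated as the Pearson correlation between the BOLD time series of predefined regions of interest (ROIs"). For the tract joining the same pair, "the mean fractional anisotropy (FA) along the reconstructed fibers will be calculated to represent the integrity of the structural pathway". The two are then combined: "Structure–function coupling will then be evaluated by assessing the relationship between FC strength and tract-specific FA values across ROI pairs". The pairs come from seven named hubs: "the insula, basal ganglia, frontal cortex, M1, SMA, corona radiata, and S1) as the primary ROI set". The association statistic is not named.

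The expected direction is stated twice. The Introduction hypothesises that the treatment "promotes microstructural repair of white-matter pathways, and strengthens structure-function coupling". The Discussion says it may enhance network integration and repair white matter, "thereby strengthening structure-function coupling across swallowing networks and facilitating functional reorganization of brain networks". The Discussion also cites a reduction of coupling after stroke, and notes a discordant case: "Improvements in functional connectivity in the absence of structural recovery may reflect compensatory reorganization rather than true restoration".

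On status, section 2.7.2 lists ALFF, ReHo, FC, FA and MD as primary and does not list coupling. The Discussion places the coupling tests within the primary, confirmatory analyses and plans to relate coupling change to clinical improvement, with healthy controls as a baseline reference.

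**The concern.** The hypothesis runs from higher FC and higher FA to stronger coupling. The measure in section 2.11.1 does not carry that step. A correlation or slope over ROI pairs ignores the level of both variables: add a constant to every FC and every FA and it does not move. What moves it is how the changes are distributed over pairs. Losses of FC and FA in the same pairs add shared variance and pull the association up; losses in different pairs pull it down. Recovery undoes whichever happened.

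A rise in coupling can therefore accompany recovery or deterioration. If it is read as benefit without looking at its components, an arm whose tracts and connectivity both worsened could be described as supporting the hypothesis, and an arm that recovered as contradicting it. Because the Discussion calls this analysis confirmatory, the mechanistic conclusion depends on the reading.

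**Working it through.** The plan gives no numerical figure for coupling, so there is none to reproduce. The check asks whether the sign of a change in coupling follows from the sign of the changes in FC and FA.

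**Inputs from the article.** FC per pair is a Pearson correlation; the structural term is mean FA per tract; seven hubs are named. Pairs: 7 × 6 / 2 = 21 if each hub is counted once, or 14 × 13 / 2 = 91 if bilateral. Which applies is an assumption.

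**Assumed inputs (not in the article).** Coupling is a within-patient Pearson correlation over 21 pairs. Intact FA is 0.45 (SD 0.05) and FC 0.30 (SD 0.15), with underlying correlation r0 = 0.3. Stroke lowers FA by 0.05 in 6 pairs and FC by 0.15 in 6 pairs (1 SD each). Further decline lowers FA by another 0.05 and FC by another 0.10 in those pairs.

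**Step 1: a six-pair example.** Before: FA 0.50, 0.48, 0.46, 0.44, 0.42, 0.40; FC 0.45, 0.50, 0.40, 0.48, 0.42, 0.47. After: the first four pairs lose 0.01 on both; the last two lose 0.12 in FA and 0.25 in FC. Every value falls (mean FA 0.450 to 0.403, mean FC 0.453 to 0.363).
- Before: r = 0.0006 / √(0.0070 × 0.00713) = 0.08.
- After: r = 0.0568 / √(0.0407 × 0.0919) = 0.93.
- The slope of FC on FA also rises, from 0.0006 / 0.0070 = 0.09 to 0.0568 / 0.0407 = 1.40. Spearman goes from 0.09 to 0.66.

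The reverse path, full recovery, takes r from 0.93 to 0.08.

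**Step 2: what decides the sign.** Let p be the damaged fraction of pairs, s the fraction damaged in both FC and FA, and a and c the losses in FA and FC in SD units. Approximately:

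r = [r0 + a·c·(s − p²)] / √{[1 + a²p(1 − p)]·[1 + c²p(1 − p)]}

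Here p = 6/21 = 0.286, p² = 0.082 and p(1 − p) = 0.204. At baseline a = c = 1, so the denominator is 1.204. After further decline a = 2 and c = 0.25/0.15 = 1.667, so it is √(1.816 × 1.567) = 1.687. With full overlap (s = 0.286):
- baseline: (0.3 + 0.204)/1.204 = 0.42;
- both decline: (0.3 + 3.333 × 0.204)/1.687 = 0.58.

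**Step 3: simulation of the same settings.** Mean coupling; repeat runs differ by about 0.01:

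| Damaged pairs shared | Intact | After stroke | Both decline further |
|---|---|---|---|
| 6 of 6 | 0.29 | 0.42 | 0.59 |
| 3 of 6 | 0.29 | 0.29 | 0.29 |
| 2 of 6 | 0.29 | 0.25 | 0.19 |
| 0 of 6 | 0.30 | 0.17 | 0.00 |

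Full recovery returns each row to its intact value: downwards in the first, upwards in the last two. Recovery of FC alone lowers coupling with full overlap (0.42 to 0.27) and raises it with none (0.17 to 0.27).

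**Step 4: sensitivity.** The overlap at which coupling stays flat depends on r0. With r0 = 0 and 3 of 6 shared, the formula gives 0.061/1.204 = 0.05 after stroke and 0.204/1.687 = 0.12 after decline, so coupling rises. A separate simulation used other assumed values (FC mean 0.40; losses of 0.10 in FA and 0.25 in FC). With 21 pairs and r0 = 0.3, shared damage to 25% of pairs took coupling from 0.28 to 0.56, and the pattern was the same with 91 pairs and with Spearman. Damage to all pairs equally left it at 0.29. Damage to independently chosen pairs lowered it from 0.29 to 0.18.

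**The case against.** The strongest reply is that the Discussion supplies the direction: it reports that stroke reduces coupling, so a rise is recovery. Where damage overlaps little, the check agrees. Stroke lowers coupling, further decline lowers it more and recovery raises it. A reader might infer from the full-overlap row that the hypothesised sign is backwards, or that compensation always weakens coupling. The article does not support either reading; both depend on an overlap that it neither states nor constrains. What remains is that the premise is a cited association, and nothing in the plan makes the reading of coupling depend on its holding in these patients.

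The second reply is that safeguards exist. FC and FA are themselves primary outcomes compared between arms, healthy controls are scanned, clinical correlations are planned, and the Discussion already describes FC gain without structural recovery as possibly compensatory. All true, so deterioration would be visible to anyone who looked. But the Discussion's caveat covers discordant change only, not FC and FA falling together, and no passage ties the interpretation of coupling to its components or to the reference value.

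Third, the statistic may be left to the full protocol or SAP. It may, and its absence is not the point. The stated inference is, and both a correlation and a slope share the problem.

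**Conclusion.** The point stands in a limited form. Stronger coupling does not follow from better FC and better FA under the measure in section 2.11.1. Joint deterioration can raise it, leave it unchanged or lower it, according to how far the two kinds of damage fall on the same pairs. In the worked settings that means 0.42 to 0.59, no change at 0.29, or 0.17 to 0.00. These magnitudes rest on assumed FC, FA and lesion values and on a within-patient correlation. The dependence of the sign on overlap does not need those particular values.

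Two stronger readings should be avoided. The direction is undetermined, not shown to be wrong. And coupling is not one of the primary outcomes in section 2.7.2; its confirmatory standing comes from the Discussion alone. It is worth correcting because it changes what may be concluded from a result the article calls confirmatory.

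**What to change.** In section 2.11.1 and the Discussion:

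1. State that higher coupling does not count as benefit on its own.
2. Use the 20 healthy controls already planned to check whether patients' baseline coupling lies below the reference, and define a favourable change as movement toward the healthy-control value.
3. Always report the change in coupling with the signed between-arm changes in mean FC and mean tract FA over the same prespecified ROI pairs.
4. Count it as support for the hypothesis only if neither component worsens relative to sham.

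The cost is small. FC and tract FA are already computed to form the measure and the control scans are already in the design, so no new data are needed. The downside is that fewer result patterns can be claimed as support. Section 2.15 reports that, at submission, the data were blinded and no primary outcome analysis had been done; the rule should be fixed while that still holds.

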#### Primary outcome

2.7.2

Derived imaging metrics will be calculated from the acquired rs-fMRI and DTI data as described below. The primary neuroimaging outcomes are defined as the changes from baseline to week 6 in prespecified rs-fMRI metrics (ALFF, ReHo, and FC) and DTI metrics (FA and MD). In addition, 20 healthy controls will undergo baseline rs-fMRI and DTI examinations to provide a reference for PSD-specific neuroimaging alterations.

Rs-fMRI: Rs-fMRI is extensively utilized to probe the neural mechanisms of PSD. The rs-fMRI markers include amplitude of low-frequency fluctuations (ALFF), regional homogeneity (ReHo), and functional connectivity (FC), which can be used to reflect brain function in patients with PSD. However, existing research primarily emphasizes activation in localized brain regions, with insufficient exploration of acupuncture's effect on functional networks in PSD patients (17).

Therefore, we employed rs-fMRI to analyze brain functional network connectivity, aiming to further clarify the central mechanisms underlying acupuncture treatment for PSD.

ALFF: ALFF reflects the local activity level of specific brain regions by calculating signal strength in the 0.01–0.1 Hz frequency band. It is commonly utilized to explore activation patterns in various brain areas, facilitating our understanding of functional changes across different regions following a stroke, particularly those related to swallowing (18).ReHo: ReHo can capture local coherence changes within swallowing-network nodes (e.g., insula, M1, SMA) in PSD by measuring the temporal synchrony between a given brain region and its adjacent voxels, thereby assessing the consistency of neuronal activity within that region (19).FC: Functional connectivity assesses the interconnections between brain regions based on correlations in temporal sequences. Seed-based analysis (e.g., bilateral insula, M1 orofacial area, SMA) and independent component analysis (ICA) employ data-driven methods to capture broader network-level modulation. Evaluating overall connectivity patterns enhances our understanding of how acupuncture may improve neural network function in PSD patients (20, 21).

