Statistical Modeling: For clinical outcomes and imaging metrics, linear mixed-effects models will be employed to assess within-subject change (baseline vs. week 6) and between-group differences (acupuncture vs. control), while adjusting for sex, age, stroke severity, and lesion volume (48). Correlation analyses will test associations between rs-fMRI/DTI metrics and clinical improvement in swallowing function (SSA/VFSS-based measures/MoCA/SWAL-QOL scales) (49, 50). This will aid in assessing whether alterations in brain networks correlate with improvements in swallowing function, thereby enhancing the clinical interpretability of imaging findings. Depending on the assumptions of normality and linearity, analyses will use either Pearson's correlation coefficient or Spearman's rank correlation coefficient.

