Therefore, in the present study we explicitly separate primary and secondary analyses. The primary (confirmatory) analyses anchor structure-function coupling tests to a prespecified ROI set that captures core swallowing-related hubs with consistent PSD abnormalities (insula, basal ganglia, frontal cortex, M1, SMA, corona radiata, and S1). The secondary (supportive) analyses extend to larger-scale circuits (DMN, frontal–temporal–sensory–motor, sensory–motor–insular–thalamic, and insula–cerebellum–occipital circuits) and are interpreted as hypothesis-generating.

DTI provides complementary insight into the microstructural substrates of PSD. The severity of white-matter injury—reflected by FA and MD metrics—is closely related to the severity of dysphagia, and adaptive white-matter changes may accompany recovery (59). Stroke is associated with disturbances of both functional and structural networks and with state-dependent reductions in functional-structural coupling (60). Therefore, this study included 20 healthy controls as a baseline reference to identify network sites with PSD abnormalities. Combined rs-fMRI and DTI analyses of SC-FC coupling sensitively index clinical impairment and recovery after PSD (46, 60).

Rs-fMRI studies indicate that acupuncture can activate swallowing-related cortical regions in PSD and enhance activity within central swallowing hubs, thereby promoting functional recovery of the cortical swallowing centers. FNIRS evidence suggests that acupuncture facilitates frontotemporal-sensorimotor network integration (61). However, PSD involves not only widespread cortico-cortical injury but also disruption of cortico-subcortical networks, and the mechanisms of structure-function reorganization remain insufficiently understood (51).

Building on this analysis hierarchy, we will examine whether acupuncture-related changes in structure-function coupling and circuit-level functional connectivity track clinical improvement over the 6-week intervention period, using healthy controls as a baseline reference.

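### ALFF and ReHo are primary outcomes, but the analysis section names them only in a whole-brain analysis it calls exploratory, and the confirmatory label goes to coupling, which is not a listed primary outcome

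*Protocol article*

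**What the plan says.** Section 2.7.2 defines the primary outcomes as "changes from baseline to week 6 in prespecified rs-fMRI metrics (ALFF, ReHo, and FC) and DTI metrics (FA and MD"). The Abstract lists the same five metrics.

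Section 2.11.1 names seven swallowing hubs and gives them a limited role, "as the primary ROI set for functional and structural connectivity tests". It defines FC by ROI pair and FA as a mean along the tract joining each pair. Then, in addition to the ROI work, "exploratory whole-brain analyses will be conducted to identify potential PSD-related brain regions beyond the predefined swallowing network". The next sentence is the only one in the analysis section that names ALFF or ReHo: "Voxel-wise comparisons of rs-fMRI metrics (e.g., ALFF and ReHo) will be performed across the whole brain between groups".

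The Statistical Modeling paragraph of the same section is general: "For clinical outcomes and imaging metrics, linear mixed-effects models will be employed to assess within-subject change (baseline vs. week 6) and between-group differences", adjusted for sex, age, stroke severity and lesion volume.

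The Discussion (section 3) sets out a hierarchy: "The primary (confirmatory) analyses anchor structure-function coupling tests to a prespecified ROI set". It repeats the exploratory status of the voxel-wise work: "exploratory whole-brain analyses will also be performed to identify potential PSD-related brain regions that may not be included in the current swallowing network framework".

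**The concern.** The same two metrics carry a primary label in section 2.7.2 and appear under an exploratory label in section 2.11.1. The ROI set that could anchor a primary test is assigned to connectivity. By the definitions in section 2.7.2, ALFF measures local activity and ReHo local synchrony, so the stated scope of the ROI set does not reach them. MD is primary too, yet it is not named anywhere in the analysis section. Coupling is called confirmatory without being a listed primary outcome.

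What is at stake is the status of the results. Once results are available, one party could point to section 2.7.2 and call an ALFF, ReHo or MD result primary, while another could point to section 2.11.1 or the Discussion and call it supportive. A reader could not settle the matter from the text. Section 2.1 says the registration was updated in October 2025 specifically to clarify the outcome hierarchy, so the sponsor itself treats these labels as important.

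**Working it through.** **Tracing each metric through the article**

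| Metric | Primary in 2.7.2 | Region or summary value stated in 2.11.1 | Where named in 2.11.1 | In the confirmatory sentence of the Discussion |
|---|---|---|---|---|
| ALFF | yes | none beyond whole-brain voxels | exploratory voxel-wise comparison | no |
| ReHo | yes | none beyond whole-brain voxels | exploratory voxel-wise comparison | no |
| FC | yes | correlation between ROI pairs | ROI connectivity and coupling | only as a component of coupling |
| FA | yes | mean along the tract between ROI pairs | ROI connectivity and coupling | only as a component of coupling |
| MD | yes | none | not named | no |
| Structure-function coupling | no | FC against tract FA across ROI pairs | ROI connectivity and coupling | yes |

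The general mixed model applies to all five primary metrics by its wording. It can be fitted to an ROI mean, a tract mean or every voxel, and the paragraph does not say which. So three of five primary metrics (ALFF, ReHo, MD) have a model but no stated quantity to put into it. One quantity called confirmatory is absent from the primary list.

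Section 2.7.2 does mention swallowing-network nodes such as the insula, M1 and SMA for ReHo. That sentence describes what ReHo can detect and does not specify a test.

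**The plan's own arithmetic**

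The only figure computed in the plan is the sample size in section 2.9: 40 × (1 + 0.15) = 46, which reproduces. No power, effect size or standard deviation is stated, and this point does not depend on any.

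**What power can and cannot show (illustration only)**

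Inputs: 20 per arm (section 2.9), a two-sided two-sample t-test, and an assumed standardized difference in change d. The voxel thresholds are also assumed, because the realized FDR threshold depends on the data.

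| Test level | d = 0.8 | d = 1.0 |
|---|---|---|
| 0.05 (one ROI test) | 69.3% | 86.9% |
| 0.05/10 | 34.2% | 57.6% |
| 0.05/12 | 31.9% | 55.0% |
| 0.001 (assumed voxel) | 17.4% | 36.3% |
| 0.0001 (assumed voxel) | 5.4% | 15.0% |
| 0.00001 (assumed voxel) | 1.4% | 5.0% |

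Ten to 12 tests corresponds to two metrics in five or six grey-matter ROIs. A full primary family is larger. Seven ROIs give 7 × 6 / 2 = 21 pairs. FC and tract FA on every pair plus 12 ALFF and ReHo tests make 21 + 21 + 12 = 54. At 0.05/54 = 0.00093 and d = 0.8, power is 16.8%, slightly below the 17.4% at the assumed voxel level of 0.001. MD on the same tracts would make 75 tests and lower power further. The ranking of ROI and voxel-wise tests therefore depends on the family size and threshold assumed.

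**The case against.** The strongest reply has three parts.

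First, a reader might infer that ALFF and ReHo are tested only by the voxel search and have no confirmatory contrast. The text does not support that. The mixed model covers imaging metrics, compares acupuncture with control from baseline to week 6, and matches the endpoint in section 2.7.2. The voxel-wise work is introduced as an addition to the ROI analyses, with ALFF and ReHo as examples. A metric can have both a primary test and an exploratory map. This part stands.

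Second, this is a condensed article, and a full protocol or analysis plan may define the regional values. That is fair for ROI extraction detail, and its absence alone would be no finding. It does not answer the conflict of labels. An unseen document cannot change the fact that the published text calls the same metrics primary in one place, names them only under exploratory work in another, and gives the confirmatory role to something else.

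Third, a reader might infer that a surviving cluster anywhere in the brain could be reported as a positive primary result. The text works against this: section 2.11.1 calls the whole-brain analysis exploratory, and the Discussion treats regions found that way as targets for later studies. Section 2.9 also calls the whole trial exploratory. What remains is narrower. Because no other ALFF or ReHo quantity is named, the primary label in section 2.7.2 has nothing definite to attach to.

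**Conclusion.** The point holds as a conflict of labels within the article, joined to an undefined primary quantity for three of the five primary metrics. It does not hold as a claim that ALFF and ReHo lack any between-group test.

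Nor do the documents show that the voxel-wise comparison is the least sensitive test for these outcomes. The power figures rest on assumed effect sizes and voxel thresholds, use the same standardized effect for a voxel and a regional mean, and lose their apparent ordering at d = 0.8 when a 54-test Bonferroni family is set against the 0.001 voxel level. They are illustrations and carry no weight in the conclusion.

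The conclusion rests on the wording of sections 2.7.2, 2.11.1 and 3 alone. It should be corrected, because it determines which results the trial may present as primary and the correction costs almost nothing.

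**What to change.** In section 2.11.1:

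- State that primary ALFF and ReHo are the mean values within the prespecified grey-matter swallowing ROIs.
- State that primary MD is the mean along the same ROI-pair tracts used for FA.
- Test each as the active-versus-sham difference in change to week 6 in the mixed model already described, within one multiplicity-controlled primary family.
- State that the voxel-wise maps cannot support a primary claim.

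If only the voxel-wise test is intended for ALFF and ReHo, move both out of the primary outcome in the Abstract and section 2.7.2. In either case, make the Discussion and section 2.7.2 agree on whether structure-function coupling is primary.

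The cost is wording plus extraction of regional and tract means from maps already produced, with no new scans. There are two drawbacks. An effect confined to a small part of an ROI is diluted in the mean, although the exploratory maps remain available for it. A larger primary family also lowers power per test, which is a reason to keep the list short. Section 2.15 says that at submission the data were blinded and no primary analysis had been done. The change should be made and dated while that is still true.

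### Multiplicity correction is named for the exploratory voxel-level and supportive network-level analyses, but not for the primary ROI tests, across the five primary metrics, or for the imaging-clinical correlations

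*Protocol article*

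**What the plan says.** Section 2.7.2 of the protocol article defines the primary outcomes as the "changes from baseline to week 6 in prespecified rs-fMRI metrics (ALFF, ReHo, and FC) and DTI metrics (FA and MD"). That is five metrics, none ranked above another.

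Section 2.11.1 sets up tiers for the imaging analyses:

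- **Primary:** seven regions, "the insula, basal ganglia, frontal cortex, M1, SMA, corona radiata, and S1) as the primary ROI set for functional and structural connectivity tests".
- **Secondary:** larger networks and circuits, which "will be reported as secondary/supportive analyses with appropriate multiple-comparison control".
- **Exploratory:** whole-brain voxel-wise comparisons. The text on these is followed by a statement that "multiple comparisons will be controlled using false discovery rate (FDR) correction (p < 0.05").

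It then closes with the general rule: "we will apply the false discovery rate (FDR) at the voxel level and Bonferroni correction for network-level metric".

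Two sets of tests come after that rule, under Statistical Modeling, with no correction mentioned. One is the set of linear mixed-effects models for the imaging metrics. The other is described thus: "Correlation analyses will test associations between rs-fMRI/DTI metrics and clinical improvement in swallowing function (SSA/VFSS-based measures/MoCA/SWAL-QOL scales").

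The Discussion (section 3) adds an inferential label: "The primary (confirmatory) analyses anchor structure-function coupling tests to a prespecified ROI set". It describes the larger-circuit analyses as hypothesis-generating. Section 2.9 describes the trial as a whole as exploratory.

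**The concern.** The correction rule and the analysis hierarchy do not fit together. The two levels at which the rule names a correction are, by the protocol's own labels, the exploratory and the supportive ones. The level that carries the primary claim, and in the Discussion the confirmatory one, has no named rule.

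This is more than detail left to an analysis plan, because the article does state a rule and does state a hierarchy. An analysis plan that followed the sentence literally would inherit the gap. With five unranked primary metrics and several regions, a nominally significant result in one region and one metric could then be presented as a primary finding without any allowance for the number of comparisons made. The same holds for a nominally significant correlation with one of the clinical scales, which would support the link between imaging and clinical improvement that the trial sets out to show.

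**Working it through.** **The plan's own figures.** The article gives no number of tests, error rate or power for this point. Its only related figure is the sample size in section 2.9, which reproduces as stated: 40 × 1.15 = 46, from a target of 20 evaluable participants per arm.

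**Inputs.** Five metrics (section 2.7.2); seven ROIs (section 2.11.1), hence 7 × 6 / 2 = 21 pairs if each region counts once; clinical measures SSA, MBSImP, PAS, MoCA and SWAL-QOL (section 2.7.3). The two-sided 0.05 level stands in section 2.11.2 for the clinical data and is assumed here to apply to the ROI tests and correlations.

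**Assumed family sizes.**

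- m = 5: one summary test per metric.
- m = 21: one test per ROI pair.
- m = 25: five metrics by five clinical scores, one correlation each.
- m = 49: ALFF, ReHo, FA and MD in seven regions (4 × 7 = 28) plus 21 FC pairs. This is hypothetical; the plan does not describe this grid.

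**Formula.** With all nulls true and independent tests, the chance of at least one false positive is 1 − 0.95^m, and the expected number is 0.05 × m. For correlated tests, m equicorrelated two-sided z-tests were simulated with 50,000 replicates.

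| m | Expected false positives | Independent | Correlation 0.5 | Correlation 0.9 |
|---|---|---|---|---|
| 5 | 0.25 | 0.23 | 0.18 | 0.10 |
| 21 | 1.05 | 0.66 | 0.43 | 0.15 |
| 25 | 1.25 | 0.72 | 0.46 | 0.17 |
| 49 | 2.45 | 0.92 | 0.62 | 0.19 |

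Every cell in the last three columns exceeds 0.05. Correlation lowers the chance of at least one false positive but leaves the expected number unchanged.

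**Effect and cost of correcting.** Bonferroni over m tests holds the family-wise error at or below 0.05; for m = 5 and independence it is 1 − 0.99^5 = 0.049. Power for a standardised difference of 0.8 at 20 per arm, by the normal approximation, is Φ(0.8 × √(20/2) − z), with z the two-sided critical value at 0.05/m. The uncorrected value is Φ(2.53 − 1.96) = 0.72.

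| m | Per-test level | Power at 0.8 SD | Difference detectable with 80% power (SD) |
|---|---|---|---|
| 1 | 0.05 | 0.72 | 0.89 |
| 5 | 0.01 | 0.48 | 1.08 |
| 21 | 0.0024 | 0.31 | 1.23 |
| 49 | 0.0010 | 0.23 | 1.30 |

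These power figures ignore covariate adjustment and the mixed model.

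**The case against.** A reader might infer that the primary tests and the correlations will be run uncorrected, and that false positives are therefore almost certain. The documents do not support either step.

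First, the absence of correction is inferred from silence, and two phrases are open in scope. The FDR sentence that follows the voxel-wise text is worded generally, and the sentence after it speaks of the interplay of structure and function, which is the coupling question. The term network-level metric is not defined, and section 2.7.2 links seed-based FC to network-level change, so Bonferroni might be meant to cover ROI-based FC. A separate analysis plan, not shown, could settle both.

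Second, the large test counts are assumptions. Section 2.11.1 ties the ROI set to connectivity tests, describes ALFF and ReHo comparisons only voxel-wise, and takes FA along tracts between ROI pairs. The confirmatory label attaches to coupling tests, which might reduce to very few. Metrics from the same brains are unlikely to be independent.

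Third, the correlations are presented as an aid to interpretation, and nothing calls them confirmatory.

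All of this stands as a limit on the size of the problem. It does not remove the problem. On the widest reading of both phrases, still no rule spans the five primary metrics or covers the correlations. The primary group comparisons use mixed models described after the correction rule, with no correction attached.

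**Conclusion.** The concern holds in a limited form: no multiplicity correction is named for the primary ROI and ROI-pair tests, across the five primary metrics, or for the imaging-clinical correlations, whereas one is named for the tiers given less inferential weight.

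The size depends on a test count that the article does not give. If tests are made at 0.05 without correction and all nulls are true, the family-wise error is about 10% to 23% for only five tests, 15% to 66% for 21 ROI pairs, and 19% to 92% for a hypothetical 49, from correlation 0.9 to independence. A type I error near 1 would need a much larger family with weak dependence, which the article does not establish.

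The labels also need reconciling. The coupling tests called confirmatory in the Discussion are not among the five primary metrics of section 2.7.2, and section 2.9 calls the whole trial exploratory.

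**What to change.** In section 2.11.1, before unblinding:

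1. Define the primary ROI family by listing its tests: the coupling tests and the ROI-level group comparisons of ALFF, ReHo, FC, FA and MD. Say how left and right are handled and which pairs are tested.
2. Control that family at 0.05 across ROIs and metrics with Holm or Benjamini-Hochberg, and say which. Holm controls the family-wise error; Benjamini-Hochberg controls the false discovery rate, a weaker guarantee for a claim labelled confirmatory.
3. Treat the imaging-clinical correlations as a separate family with false-discovery-rate control, or report them as exploratory.
4. Keep the existing voxel-level and network-level rules.
5. If the ROI family is not controlled, drop the confirmatory label from the Discussion, in line with section 2.9.

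This is a change of wording. Section 2.15 reports that at submission the data were blinded and no primary outcome analysis had been done; a rule chosen after unblinding would carry little weight.

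The cost is power per test: with Bonferroni, for a 0.8 SD difference at 20 per arm, from 0.72 to 0.48 over 5 tests and 0.23 over 49. Holm is never less powerful than Bonferroni. A short family is therefore worth having. Naming a single primary endpoint would save more power, but it would change the outcome hierarchy whose registration was already updated on 30 October 2025 (section 2.1), so it is a trade-off for the sponsor and not needed to close this gap.
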